## 2. Design & Methods

### 2.1. Study aims and study design

This interdisciplinary, Germany-wide study examines a) the multifaceted impacts of EOtC by combining expertise from the fields of public health, ecology, pedagogy, special needs education and social sciences, and b) possible connections between constructs across these domains in the context of EOtC. The study follows a parallel multi-strand research approach, combining independent quantitative and qualitative sub-studies within an overarching framework. This exploratory, quasi-experimental study will be conducted in schools throughout Germany.

#### 2.1.1. Aims and design of the health-related study component.

The health-related objective of this study is to examine how regular participation in EOtC is associated with psychological, physiological, and behavioural indicators of health among teachers and pupils. Regarding teachers, this study component investigates whether EOtC contributes to improved reduction of physiological stress, emotional well-being, and higher PA by comparing EOtC and classroom teaching days within individuals. Additionally, WRQoL is assessed between teachers who regularly implement EOtC and those who exclusively teach inside the classroom. Regarding pupils, the study explores potential links between EOtC and cognitive functioning, emotional regulation, and stress. It also investigates basic psychological needs (BPN) and nature connectedness as distinct psychological correlations of school-related well-being.

The health-related measurements of the project follow a cross-sectional, quasi-experimental design and are embedded in a broader, cross-disciplinary mixed-methods evaluation, which will be further explained later.

#### 2.2.2. Aims and design of the ecology-related study component.

To assess the role of EOtC in *Education for Sustainable Development* (ESD) the key components knowledge, nature connectedness and appreciation of nature will be assessed, as they are known to promote pro-environmental behaviour and attitude [25,26]. The aim of the ecological component of this study is therefore to understand how regular EOtC improves the nature connectedness and appreciation of nature in pupils and teachers, as well as the knowledge of species. In addition, biodiversity and structural characteristics of the learning sites will be systematically recorded, providing the basis for exploring how variation in ecological richness related to educational and health-related outcomes.

The ecological questionnaires are collected in longitudinal surveys twice per school year and are also included in the cross-disciplinary, mixed-methods evaluation. In addition, the biodiversity of the outdoor learning areas at selected schools will be mapped once during the school year and combined with data from ecological, health and sociological surveys.

#### 2.2.3. Aims and design of the social interaction and special needs-related study component.

The pedagogical component of this study focuses on the types of interactions between teachers, pupils, and learning objects during EOtC lessons, with particular attention to the promotion of pupils with special educational needs. Using a reconstructive, qualitative analysis of video recordings from both classroom teaching and EOtC, this study investigates how teaching and learning processes emerge, or fail to emerge, depending on the environment.

On the teacher’s side, particular attention is paid to how they engage with the changed spatial conditions of EOtC. The core research question is whether changes occur in teachers’ instructional behaviour when moving from a structured classroom environment to an unstructured outdoor learning environment and how these changes look like. Furthermore, the study aims to identify different teaching styles and strategies that may either promote or hinder students’ learning processes in EOtC. On the pupils’ side, the focus lies on the nature of their interactions with teachers, peers, and learning materials. The guiding question here is whether leaving the structured classroom environment results in qualitative changes in these interactions. As an additional perspective, resonance theory [27] will be used to explore whether EOtC fosters moments of resonance and reduces experiences of alienation, particularly among pupils who often struggle to engage in classroom lessons.

In this context, resonance is defined as a reciprocal relationship between subject and world, comprising four key dimensions: (a) being affected, where the subject feels addressed by the world and is moved by something; (b) an agentic response, in which the subject responds with their own voice and a sense of agency; (c) transformation, referring to a process of mutual transformation (“Anverwandlung”, German) between subject and world that results in change; and (d) unavailability (“Unverfügbarkeit”, German), meaning that this process is neither predictable nor fully controllable by either side [27].

This model (particularly dimensions a–c) can be applied to school-based learning and ideal-typical learning phases to describe barriers within the learning process [28]. The dimensions of resonance will be used as an analytical framework for empirical video data, functioning as sensitizing concepts [29], in order to reconstruct interaction patterns and teaching–learning processes from a resonance-theoretical perspective.

Furthermore, this study aims to identify core pedagogical principles and structural features which characterize EOtC in contrast to traditional classroom instruction.

### 2.2. Setting – the German school system

Schooling in Germany begins with primary education (grades 1–4), typically starting at the age of six. This is followed by the secondary system, where pupils are either allocated to different school types based on their academic performance or parents are free to choose a school for their child, depending on the regulations of the respective federal state. Although education policy and curricula are the responsibility of the individual federal states, overarching educational standards are set by the Standing Conference of the Ministers of Education and Cultural Affairs (Kultusministerkonferenz) to ensure national comparability. Schools can be publicly, privately, or denominationally funded, but are all legally obliged to implement the state-specific curricula and educational guidelines [30]. Therefore, both primary and secondary schools, as well as special needs schools throughout Germany can be included in the sample, provided they meet the inclusion criteria.

### 2.3. Recruitment process and participants

As mentioned above, EOtC is defined as regular, curriculum-based teaching, which is conducted in a natural, cultural, historical or urban environment [11,14]. This definition builds the base for inclusion and exclusion criteria when identifying schools, classes and teachers to participate in this study. Schools were included in the study if EOtC was carried out for at least four hours every two weeks. This threshold was chosen to ensure that participating classes engage in EOtC for approximately one full day per week in the case of elementary school and at least half a school day in the case of secondary schools. No additional exclusion criteria were defined. The frequency is intended to emphasize that EOtC is not a sporadic activity, but rather a consistent and integral element of the pupils’ and teachers’ routine. Schools in all of Germany’s federal states were contacted in order to represent as many federal states, school types and associated learning locations as possible. A total of three different sources of contact were used to recruit schools for data collection: Some contacts already existed to individual schools implementing EOtC in Germany through previous projects and conference attendance by individual scientists. Similar collaborations with schools already existed with the external project partner, Schutzgemeinschaft Deutscher Wald (SDW). In addition, an internet search was carried out for schools which have implemented the concept of EOtC. In the recruitment phase from beginning of January to the end of July 2025, 101 schools were initially contacted. Of these, 45 schools showed interest. 13 schools actively declined, citing reasons such as lack of time, insufficient capacity or no specific reason. Four schools did not meet the inclusion criteria. 43 schools did not respond at all. Five schools withdrew after initially agreeing to participate, resulting in a final sample of 36 schools. A flowchart mapping the various stages of recruitment, number of excluded and included schools, as well as reasons for inclusion/exclusion and the numbers of participating pupils and teachers is shown in Fig 1. To obtain a precise overview of the classes, pupils and teachers involved, network meetings were held at which the planned surveys were first presented, and the interest of the individual teachers was then queried. Emails were sent to the schools that were unable to attend the meetings to obtain a final sample size. In addition to EOtC classes and teachers, corresponding control classes and teachers were also sought at each participating school to include them in the data collection as both intra- and inter-individual comparisons are planned in the study design.

**Fig 1 pone.0337524.g001:**
[figure not shown]
Stages of recruitment.

This results in expectedly 36 schools with approximately 50 EOtC teachers, 50 non-EOtC teachers, 50 EOtC classes, and 18 non-EOtC classes (Fig 2). All participants provide written informed consent prior to taking part in the study. Each participant receives detailed written information about the study’s aims, procedures, and data protection measures. In the case of child participants, written consent is obtained both from the children themselves (age-appropriate assent) and from their parents or legal guardians. All data are pseudonymized using individual participant codes, which are self-generated by the participants to ensure confidentiality. The research team has no direct access to personal identifiers.

**Fig 2 pone.0337524.g002:**
[figure not shown]
Schematic representation of the study locations in Germany. Base map adapted from Wikimedia Commons (public domain).

### 2.5. Measures Health

#### 2.5.1. Teachers’ background and self-efficacy.

To collect the necessary background data on teachers, both their teaching experience in years and their self-efficacy will be assessed. Work experience is recorded by asking a single question about the number of years of teaching experience in this position. The *Scale for Teacher Self-Efficacy* (STSE) [31] is used to measure the self-efficacy in their profession. It’s the validated German questionnaire of the short version of the ‘Teachers’ Sense of Efficacy Scale’ by Tschannen-Moran and Hoy [32]. The questionnaire consists of three scales, inquiring about instructional strategies, class management and student motivation. Each scale comprises four items and will be rated on a nine-point Likert-scale, ranging from not at all convinced to completely convinced.

#### 2.5.2. Teachers’ physiological stress.

Physiological stress will be measured by salivary cortisol, a validated biomarker of the hypothalamic–pituitary–adrenal axis (HPA) activity that has previously been applied in educational settings [17,33,34]. Saliva samples will be collected by the teachers themselves using Salivettes^®^ (Sarstedt, Germany), with individual sampling kits provided to all participants to ensure standardized collection. To account for intra-individual variability in cortisol secretion, a repeated-measures design will be used. The sampling will be conducted on four separate days, comprising two days of EOtC sessions and two days of classroom teaching. On each day, the cortisol awakening response (CAR) will be measured as an individual baseline reference. This includes one saliva sample immediately upon awakening and a second sample 30 minutes later for men and 45 minutes later for women to capture the peak cortisol level. The adjusted timing accounts for gender-specific differences in the temporal dynamics of the cortisol response to awakening [35,36].

In addition, three daytime samples will be collected on each measurement day at standardized time points (8:00 AM, 10:15 AM, and 12:30 PM) to determine the diurnal cortisol pattern and allow comparisons across days and conditions. After collection, samples will be stored during the day in the provided insulated bag and frozen in a household freezer in the evening prior to collection by study staff. To account for potential confounding effects of sleep duration and sleep quality on cortisol secretion, sleep-related variables will be assessed separately.

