Even though existing research already highlights important effects of EOtC on pupils, further questions remain unanswered. For example, how different EOtC environments may influence pupils’ knowledge, basic psychological needs, nature connectedness and social interactions, as well as those with nature. It is important to understand how pupils interact not only with the environment but also with their classmates, as these interactions influence not only individual outcomes but also the overall learning environment. Furthermore, most research to date has focused primarily on the impact of EOtC on pupils, while teachers and the demands of their work environment have received comparatively little attention.

Therefore, this EOtC study is an interdisciplinary research project, aiming to investigate the potential effects of regular EOtC on health-related, social, pedagogical, and ecological outcomes in German schools and to examine how these outcomes are interrelated across these domains where possible. Given this thematic range and methodological approach, the study addresses a set of research questions structured across four key domains, which are outlined below.

Health-related research questions:

1. Can intra-individual differences in diurnal cortisol dynamics, specifically the subsequent decline throughout the school day, be observed in teachers on EOtC days compared to regular indoor teaching days?2. What differences in teachers’ hedonic well-being, particularly in terms of positive and negative affects, can be observed on EOtC days compared to regular indoor teaching days?3. What differences in teachers’ physical activity and sedentary behaviour can be observed on EOtC days compared to regular indoor teaching days?4. To what extent is higher work-related quality of life (WRQoL) observed among teachers participating in EOtC compared to those teaching exclusively in indoor settings?5. How do children’s EEG patterns related to attention, stress, and emotional regulation differ between EOtC and regular indoor teaching days?6. Is there another dimension in the construct of BPNs that addresses the fulfillment of the need relatedness through a non-social factor, namely nature relatedness?7. Which effects do BPNs and/or nature relatedness, if considered a separate construct, have on children’s school-related well-being?

Pedagogical research questions:

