### 2.8. Data analysis

#### 2.8.1. Statistical analysis.

To evaluate the quantitative data of WRQoL, emotional well-being, psychological well-being, nature connectedness, appreciation of nature, PA and SB descriptive analyses will be carried out, in order to present central tendencies and distributions of the variables collected. Inferential statistical methods and repeated measures analysis of variance will be used to test group differences and hypotheses. To make sure the data structure enables this procedure, the data will be checked for normal distribution and homogeneity of variance before the analysis.

To investigate the relationship between the ecological features of the learning environments and other study variables correlation analyses, linear regression models and possibly generalized linear models or mixed-effect models will be used in order to take possible hierarchical structures of the data into account.

Linear mixed models will be used for the cortisol measurements to adequately account for intra-individual changes and covariates such as sleep quality or chronotype. In addition to descriptive analyses of the collected data, Bayesian Hierarchical Linear Models will be used to investigate the influence of PA and SB on cortisol levels.

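### The same-day awakening response is the cortisol baseline, so any EOtC-versus-classroom difference in the morning peak would pass straight into a decline measured from it

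*Protocol article*

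**What the plan says.** - **Target.** Health question 1 (protocol article, section 1) asks about the diurnal cortisol course, "specifically the subsequent decline throughout the school day, be observed in teachers on EOtC days compared to regular indoor teaching days".
- **Baseline.** Section 2.5.2: "On each day, the cortisol awakening response (CAR) will be measured as an individual baseline reference". It consists of a sample on waking and "a second sample 30 minutes later for men and 45 minutes later for women to capture the peak cortisol level".
- **Days.** "The sampling will be conducted on four separate days, comprising two days of EOtC sessions and two days of classroom teaching". The baseline is therefore taken afresh on each of the four mornings.
- **School-hours samples.** In addition, "three daytime samples will be collected on each measurement day at standardized time points (8:00 AM, 10:15 AM, and 12:30 PM"). The same sentence gives these samples the purpose of describing the daily pattern and of comparing days and conditions.
- **Interpretation.** Section 2.1.1: "this study component investigates whether EOtC contributes to improved reduction of physiological stress".
- **Model.** Section 2.8.1: "Linear mixed models will be used for the cortisol measurements to adequately account for intra-individual changes and covariates such as sleep quality or chronotype".

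The article does not say whether the awakening response is subtracted, used as the start of the slope, entered as a covariate or analysed separately.

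**The concern.** A baseline for a within-person comparison should not be open to influence from the condition being compared. Sections 1 and 2.3 describe EOtC as a regular part of the timetable, so a teacher will normally know on waking whether an EOtC day or a classroom day lies ahead. The waking and peak samples come before school but not before that knowledge. They are day-specific responses, not a stable property of the teacher.

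The baseline includes the day's peak, and question 1 concerns the decline that follows. The natural reading is therefore a decline measured from that peak. On that reading, a higher peak on one type of day gives a steeper decline on that type of day, whatever happens at school. Because the aim is framed as better stress reduction, a more activated morning could be reported as better recovery during the EOtC day. A lower peak on EOtC mornings could equally hide a real benefit.

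**Working it through.** The article gives no cortisol effect size, standard deviation or power, so there is no stated figure to reproduce. From the documents come the sampling times, two days per setting and about 50 EOtC teachers (section 2.3). All concentrations, waking times and standard deviations below are assumptions.

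**1. Decline from the peak.** Let P be the peak and L the 12:30 value. If L is the same in both settings and the EOtC peak is P + d, then

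[(P + d) − L] − [P − L] = d.

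The contrast equals d exactly, whatever its sign.

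**2. One example.** Assume a woman who wakes at 06:00, so the second sample is at 06:45, with 10 nmol/L at 08:00 and 5 at 12:30 on both day types.
- Classroom day, peak 15: (15 − 5)/5.75 = 1.74 nmol/L per hour.
- EOtC day, peak 18: (18 − 5)/5.75 = 2.26 nmol/L per hour, and 2.26/1.74 = 1.30.
- 08:00 to 12:30 on both days: (10 − 5)/4.5 = 1.11 nmol/L per hour.

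**3. Least-squares slope through peak, 08:00, 10:15 and 12:30.** With times 6.75, 8, 10.25 and 12.5 h, the mean is 9.375 and the sum of squared deviations is 19.3125. Raising only the peak by d changes the slope by −2.625d/19.3125 = −0.136d. For an assumed profile of 18/10/7/5 nmol/L the base slope is −2.03.
- d = 1: −0.136 (7% steeper).
- d = 2: −0.272 (13% steeper).
- d = 4: −0.544 (27% steeper).

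**4. How often this would reach significance with 50 teachers and 2 + 2 days.**
- *Log scale.* Assume a peak 0.15 log units higher on EOtC days, a residual SD of 0.35 and no daytime difference. The SE of the within-teacher contrast is 0.35 × √2/√50 = 0.07, and 0.15/0.07 = 2.14 against a cut-off of 2.01. A significantly steeper EOtC decline is expected in about 56% of studies (noncentral t, 49 df); simulation of 2,000 runs gave 57%. Measured from 08:00 instead, it was about 3%, against a nominal 2.5% in one direction.
- *Original scale.* Assume SDs of 2 between teachers, 1.5 between days and 4/2.5/2/1.5 within day, with a paired t-test at two-sided 0.05 and 3,000 runs:

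| Peak excess d (nmol/L) | Peak minus 12:30 | Slope from peak | Slope 08:00–12:30 |
|---|---|---|---|
| 0 | 4.7% | 4.8% | 5.4% |
| 1 | 36% | 32% | 4.6% |
| 2 | 90% | 85% | 5.1% |
| 4 | 100% | 100% | 4.4% |

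**5. Awakening response as a main-effect covariate.** Its value is constant within a day. With complete data it therefore cannot change the time-by-setting slope. In one simulated data set the slope term was −0.0217 with and without the covariate. The level term does move: with equal daytime levels, a CAR difference d and coefficient b, the adjusted setting difference is −b × d. In the same data set it went from 0.038 to 0.023.

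**6. Carry-over to 08:00.** If half of d = 2 persists at 08:00, that value rises by 1 nmol/L. The 08:00–12:30 slope then changes by −2.25 × 1/10.125 = −0.222 nmol/L per hour, which was significant in 66% of runs. The mean daytime level is then higher by 1/3 nmol/L.

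**7. Named covariates.** Chronotype is measured once and is constant within a teacher, so it cannot explain a difference between that teacher's days. Sleep quality is recorded each morning but does not measure anticipation of the day ahead.

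**The case against.** The strongest reply is that no passage says the decline is computed from the peak. Section 2.5.2 gives the purpose of comparing conditions to the three school-hours samples, and these fit the window in question 1. On that reading most of the problem disappears, and how the awakening response enters the model is a detail that an unseen analysis plan may settle. This stands in part: the exact use is open, and the missing formula is not itself the finding. What remains is that the article does name the same-day awakening response as the baseline reference, and nothing in it limits that role.

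Several stronger readings are tempting but not supported.
- *That teachers do wake more activated on EOtC days, so the result will favour EOtC.* The documents report no anticipatory difference. EOtC is routine for regular participants, and the difference could run either way.
- *That every use of the awakening response makes the decline look steeper.* As a main-effect covariate it leaves the slope contrast alone (step 5).
- *That the 56% or 57% is the false-positive rate of the planned analysis.* It describes one possible endpoint under an assumed peak difference.
- *That the article defines a steeper slope as improvement.* Section 2.1.1 states an aim, not a scoring rule.

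It is also fair that moving to 08:00–12:30 is not complete protection (step 6).

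**Conclusion.** The point holds as a conditional one. The stated baseline is measured on a morning when the day type is normally known, so its independence from setting cannot be taken for granted. If question 1 is answered with a decline or change from the peak, any peak difference between day types enters one-for-one, in either direction. If the awakening response is a main-effect covariate, the daytime level contrast is affected and the slope contrast is not.

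Only the algebra is certain. For assumed peak differences of 1 to 4 nmol/L, the slope from the peak would change by about 7% to 27%, and the two-point example with 3 nmol/L gives 30%. The significance rates of 32% to 100% depend wholly on the assumed differences and standard deviations. The study is exploratory, but this is its physiological result on teacher stress, and the change costs little enough that it should be made before the cortisol data are analysed.

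**What to change.** - Estimate the question 1 decline from the 08:00, 10:15 and 12:30 samples, as the time-by-setting term in the linear mixed model already planned. Do not subtract the same-day awakening response or use its peak as the origin of the slope.
- Analyse the awakening response (second sample minus first) as a separate outcome by day type, so that any difference before school is seen and not absorbed.
- Report the daytime level, including the 08:00 value, beside the slope, because a morning excess that lasts to 08:00 would still steepen the 08:00–12:30 slope.
- Describe a steeper slope as better stress reduction only if the daytime level is not higher on EOtC days.

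This needs wording in the analysis section only, and no additional samples. The downside is that two cortisol results are reported instead of one.
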